### Ethics and dissemination

This study is approved by the Swedish Ethical Review Board (reference number 2019–03347) in Gothenburg. Since participants are adolescents aged <15 years, consent from both parents (all parents if eligible) and the adolescents themselves will be obtained, as required by applicable laws and regulations.

This study is based on a validated programme that has been conducted in other countries showing good preventive effect. Based on previous studies, we expect preventive effects of the intervention in the participating adolescents. To ensure that the risks are minimal throughout the programme implementation and follow-up, we will provide all participants from the preintervention phase through postintervention follow-up, in both control and intervention arms, with access to professional help in the form of psychologists, doctors and nurses if needed. The research group has solid experience implementing the treatment programme in other settings; their experience indicates that the intervention is perceived as positive by students and that participation in the group work has not been stigmatising. All measures and assessments used in the study are validated and tested in many other studies. All researchers and professionals in this study have good paediatric psychiatric competence. They are accustomed to talking with adolescents and will be able to carefully and sensitively handle unpredictable situations. All personnel involved in the study undergo training in the intervention. The research team is trained in good clinical practice (GCP) (scientific quality and ethical standards for planning, conducting, recording and reporting trials involving human participation). The study subjects will never be alone during the intervention because the intervention is carried out in groups and by trained staff. We will ensure the privacy of study participants, and all relevant legislation will be followed regarding use of research data. All members of the research group have undergone training in the intervention by the founders of the programme. The research group consists of general practitioners, psychologists, specialist nurses and social workers. The trial manager is a specialist psychologist and a PhD, and the implementation leader is a specialist nurse and PhD. The founders of the programme are both professors of psychology, one in the USA and the other one in Iceland.

Results from the study will be presented so that no individuals, including students, parents and the employer representatives, will be identifiable. All results will be presented on a group level. All participation is voluntary, and the student can withdraw from the study at any time.

The trial will be conducted in compliance with this study protocol, the Declaration of Helsinki and its modifications, and GCP.

We plan to disseminate the knowledge gained from this study by publishing our results in peer-reviewed scientific journals, giving presentations at national and international conferences, and spreading information through local and national media channels. We will approach local and national politicians to ensure prolongment of the project.

## Discussion

The study protocol of this research project shows that the planning and organisation of the research make it feasible to answer the four research questions.

Question (1). Is the Thoughts and Health programme feasible in the context of Swedish schools, from the perspective of the students participating in the programme? The answer will be based on the qualitative interviews and focus group discussions conducted with adolescents participating in the intervention group, as well as analysis of the course surveys gathered after each session and analysis of possible dropouts.

Question (2). Is the Thoughts and Health programme feasible in the context of Swedish schools, from the perspective of the primary care professionals leading and supporting the programme implementation? The answer will be based on the analysis of interviews with the professionals who have taken part in individual interviews after the completion of the intervention course, as well as analysis of the course surveys gathered after each session.

Question (3). Does participation in the Thoughts and Health programme have an effect on the development of depressive symptoms? The answer will be based on collected data and statistical analyses. Outcomes will be collected before, at and after baseline, based on adolescents’ and adults’ reports. Comparisons of effect sizes will be made between the arms of the study (control schools and intervention schools). Measures are described in the protocol and in table 2.

Question (4). Will participation in the course Thoughts and Health increase the participants' chances of completing middle school with high school eligibility? The answer will be based on follow-up measurements of completion and final grades at graduation from middle school. Comparisons of effect sizes will be made between the arms of the study (control schools and intervention schools).

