Most programmes aimed at preventing depression have included both youth who have suffered a prior depression and those who have never been depressed. The study of prevention of relapse or recurrence in prevention programmes for those who have already suffered an MDD is clearly useful, but earlier studies have not distinguished between prevention of the first episode of MDD and the prevention of relapse/recurrence of MDD. However, because of the recurrent nature of the disorder and the differing causal factors and probability patterns of first versus subsequent episodes^17^ and in order to prevent the deleterious effects of an episode of MDD on youth, it is especially important to study the prevention of the first or initial episode among never previously depressed subjects.

Since clinical depression among adolescents increases significantly at about the age of 15 years, and Swedish children finish their compulsory school (junior high school) at that age, being at risk of depression can be a reason for failing their final examinations, thereby limiting their chances for further academic studies.

We would like to test the feasibility of implementing the Icelandic method in a Swedish context and to evaluate the long-term effects of such a programme. We would like to test the method with a quasi-experimental controlled trial and to evaluate the outcomes after 6, 12 and 18 months. The control group will be assessment-only adolescents; they receive ordinary ‘Student Health’; they participate in all study assessments, but they are not offered the intervention Thoughts and Health.

This is, to our knowledge, the first study in Sweden that employs a longitudinal design to evaluate the effects of a school-based programme aimed at preventing depression in adolescents.

This study will be implemented together and within the municipalities of Tjörn and Orust, two islands off the west coast of Sweden, with each island having only two middle schools. Thus, this study is built on a close collaboration between academia, primary care and the community.

We are hopeful that this programme will be transferrable to a Swedish context and that it will be possible to further develop and enhance the method. Although Iceland and Sweden are similar in many ways, the school system and cultural context differ to some extent.

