### Participants

An invitation regarding participation in the study to high schools in the area resulted in four junior high schools from the municipalities of Tjörn (Häggvall and Bleket, intervention arm) and Orust (Henån och Ängås, control arm) that will participate in the study. The allocation of the schools was chosen on the basis of their rural location and socioeconomic similarity, willingness to participate and available staff. Since all schools had shown interest in participating in this study, the assignment of intervention and control arms was determined on the basis of available resources; therefore, Tjörn was chosen for the intervention programme at this stage. Two intervention courses were planned (I and II), with course I beginning at the start of the fall semester (~1 September) 2019 and course II beginning at the start of the fall semester (~1 September) 2020.

In total, approximately 320 eighth grade Swedish adolescents aged 14 years will participate in a preintervention screening process per course. In the preintervention screening process, all students will complete the Children’s Depression Inventory (CDI, described further)^19^ assessment instrument via an online questionnaire tool. This will be part of the existing “Student Health” ordinary assignments that include health and mental health status checkups as per the Swedish School Law.

We are aware of the small number of students that will be part of the collected data at this early stage, and we are planning a full-scale randomised trial once we have completed this first study; hence, there were no power calculations of sample size at this stage.

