### Intervention: prevention programme

The prevention programme will be based on the Icelandic Thoughts and Feelings programme^1^ and will include 12 group sessions of 90 min duration, delivered two times per week for 2 weeks and then once a week for 8 weeks in the school setting by Student Health school psychologists. School nurses will also attend each session as support for the students. The programme uses two intervention manuals: a group leader manual and a student manual. Both of these manuals have been translated first from Icelandic to English, and then from the English version into Swedish, and finally corrected for language in the Swedish version. After translation, the manuals were additionally reviewed by several eighth-grade students for cultural acceptability (eg, word choice) and adapted as per their feedback. The course material is based on cognitive behaviour theory, and the course will be held as a group activity. The course was originally developed as a group activity, and we will test this method in our study, as part of the evaluation of whether the method is suitable for Swedish adolescents of today. The course contains group sessions focusing on a specific topic, after which they will describe their state of health and feelings in a diary and receive some home assignments to be completed between sessions. All sessions start with a light refreshment and a summary of the previous session. Session #1 is an introduction. Session #2 is about ‘the spiral’, that is, how negative or positive thoughts and actions affect subsequent actions and feelings. Session #3 is about relaxation. Session #4 will discuss the concept of a ‘baseline’. The remaining sessions deal with the following topics: setting targets (session #5), feelings (session #6), negative thoughts (session #7), irrational thoughts (session #8), self-perception (session #9), communication (session #10), stop and reconsideration (session #11) and course consummation (session #12, final session).

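### Each arm is one municipality, so no analysis can separate the programme's effect on depressive symptoms or school completion from differences between the islands, yet the article says these questions can be answered

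*Protocol article*

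**What the plan says.** **Allocation.** The Participants section places two schools from Tjörn in the intervention arm and two from Orust in the control arm. The Introduction confirms there are no others to draw on: "each island having only two middle schools". Participants then says that "the assignment of intervention and control arms was determined on the basis of available resources", and so "Tjörn was chosen for the intervention programme at this stage".

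**Delivery.** The Intervention section describes "12 group sessions of 90 min duration" and says that "the course will be held as a group activity". Controls receive ordinary Student Health and the study assessments, so course groups exist in one arm only.

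**Analysis.** The Statistical analysis section names t-tests and chi-square tests for baseline, a Cox model for depressive symptoms, parental depression as a moderator, and stratification by student characteristics. It mentions no term or variance correction for school, course group or municipality. It names no test for grades.

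**Claims.** The Discussion says that "the planning and organisation of the research make it feasible to answer the four research questions". For questions 3 (depressive symptoms) and 4 (school completion) it says "Comparisons of effect sizes will be made between the arms of the study (control schools and intervention schools"). The strengths and limitations box says the design will inform on whether the programme prevents depressive episodes, and ties the lack of randomisation and the small numbers to generalisability alone.

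**The concern.** Arm and municipality are the same variable. Any difference between the two islands in grading practice, in the ordinary Student Health service or in local events during follow-up is part of the arm contrast. This is a threat to bias, and a wider interval does not remove it. It bears most directly on question 4, because grades are awarded by the schools themselves.

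A second, lesser matter is precision. Students in the same school, and those in the same course group, tend to resemble one another. If the named student-level methods are used without allowing for this, the intervals are too narrow.

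At stake is what the study may conclude on questions 3 and 4. As worded, the article gives a reader grounds to treat a difference between two islands as evidence that the programme prevents depression or improves school completion.

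**Working it through.** The article gives no power, alpha or intraclass correlation (ICC), so there is no figure of its own to reproduce.

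**Step 1: level of allocation.** There are two municipalities, one per arm (Participants). Degrees of freedom for the arm effect at that level: 2 units − 2 arm means = 0. The between-municipality variance can be neither estimated nor removed from within the study. To show that a small component matters: with n = 40 per arm and a municipality ICC of 0.01 (assumed), the variance ratio is 1 + (40 − 1) × 0.01 = 1.39. A nominal 5% test then has a true error of 2 × (1 − Φ(1.96/√1.39)) = 9.6%.

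**Step 2: clustering by school, if uncorrected.** Inputs:
- 40 students per arm: the expected figure in Participants, taken as the total over both courses. This agrees with about 20 intervention students per course × 2 courses.
- Even split over two schools: assumed, giving m = 40/2 = 20 per school.
- Course I only: about 20 per arm, so m = 10. Current trial status expects the last 18-month follow-up in April 2021, while Participants starts course II in about September 2020. An analysis at that date can therefore hold 18-month data from course I only.
- ICC: assumed, 0.02 to 0.10.

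Design effect DE = 1 + (m − 1) × ICC. True error of a nominal 5% test = 2 × (1 − Φ(1.96/√DE)). This is the standard approximation for means and proportions, used here as a guide for the Cox model.

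| ICC | m = 20: DE | true error | m = 10: DE | true error |
|---|---|---|---|---|
| 0.02 | 1.38 | 9.5% | 1.18 | 7.1% |
| 0.05 | 1.95 | 16.0% | 1.45 | 10.4% |
| 0.10 | 2.90 | 25.0% | 1.90 | 15.5% |

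The standard error is understated by √DE: a factor of 1.17 to 1.70 at m = 20. If the 40 per arm were instead meant per course (80 per arm, m = 40), the error would be 14.2% to 37.6% over the same ICC range.

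**Step 3: course groups, in one arm only.** With group sizes of 10 to 20 and ICC 0.02 to 0.10 (all assumed), the standard error factor is √((DE + 1)/2). At size 10 and ICC 0.02 it is √((1.18 + 1)/2) = 1.04, with true error 6.0%. At size 20 and ICC 0.10 it is √((2.90 + 1)/2) = 1.40, with true error 16%.

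**Step 4: what a school-level comparison can offer.** Four schools less two arm means leave 2 degrees of freedom, with critical value 4.30 against 1.96. Combined with √DE at m = 20, the interval is (4.30/1.96) × 1.17 ≈ 2.6 times the naive width at ICC 0.02, and (4.30/1.96) × 1.70 ≈ 3.7 times at ICC 0.10. Even this treats the schools within a municipality as independent, so it does not reach the problem in step 1.

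**The case against.** The strongest reply is that this is a feasibility study that admits its limits. Feasibility is the primary question and the effect questions are secondary. Participants concedes small numbers, explains that no power calculation was made, and announces a full-scale randomised trial. The box names the absence of randomisation. Schools were chosen for rural location and socioeconomic similarity, and baseline comparisons and stratification are planned. The Discussion's wording could also be read as a statement about logistics.

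Much of this stands as context, but it does not remove the point. Similar schools and baseline comparisons reduce the expected difference between the islands without making it separable from the arm effect. Neither clustering nor the identity of arm and municipality is named anywhere. A purely logistical reading is hard to keep when the Introduction states effect hypotheses, the box speaks of prevention, and Current trial status calls the 18-month follow-up the primary endpoint.

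A reader might also infer that the plan declares students independent and that its intervals are certain to be too narrow. The article does not say so. It is silent on clustering, and an analysis plan that is not shown may add a robust variance or a school term. The precision point is therefore conditional. For grades it is weaker still, because no test is stated that could be called wrong. Nor do the documents show that a difference between the islands will in fact be reported as a programme effect; the present wording only leaves room for it.

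**Conclusion.** The point holds for secondary questions 3 and 4. The Discussion and the strengths and limitations box claim for the effect questions something that the design cannot give. This rests on stated facts (one municipality per arm, non-random assignment) and needs no assumed figure. An unseen analysis plan could correct the variance but could not separate arm from municipality. Because rewording costs little and changes what may be concluded, it should be done before results are reported.

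The clustering figures are illustrations, conditional on no correction being made: a true error of about 9.5% to 25% at 20 per school and about 7% to 16% at 10 per school. They depend on the assumed ICC of 0.02 to 0.10, on 40 per arm and on an even split. The direction holds for any positive ICC.

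Two stronger readings are not supported. Adjusting for school would not rescue the comparison, since the confounding lies one level higher. And the primary questions on feasibility do not rest on the arm contrast, so they are not affected.

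**What to change.** 1. **Reword the Discussion and the strengths and limitations box.** Say that questions 1 and 2 will be answered as planned. Say that questions 3 and 4 will give preliminary estimates with 95% confidence intervals, and that the arm effect cannot be separated from municipality. Name internal validity as limited, alongside generalisability. State that no claim of prevention or of improved school completion will be drawn from the arm comparison alone.

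2. **As a supporting step, show results by school, two against two.** Where student-level intervals are given, allow for school and, in the intervention arm, for course group, with small-sample degrees of freedom. State beside them that this does not remove confounding by municipality. Two schools per arm barely identify a school variance, so the school-by-school display matters more than the model.

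3. **Past completion rates: descriptive background only.** Earlier whole-school rates may be shown to indicate how far the islands already differ. They should not be used in a difference-in-differences for participants: participants are selected at or above the 75th percentile on the CDI and then screened for diagnoses, while school totals cover whole year groups. It would still compare one municipality with one.

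Cost: some rewording, wider intervals and a more modest conclusion. No more participants are needed.

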### Current trial status

Recruitment of participants started in September 2019, and the last participant is expected to reach the primary endpoint (18-month follow-up) in April 2021. Primary data analysis will begin in May 2021. The naturalistic follow-up phase of the trial will continue until October 2022.

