**Methods and analysis:**

A quasi-experimental controlled design, combined with qualitative and quantitative methods, will be used to address the research questions.

In this study, 617 children aged ~14 years will be screened for depression, and those “at risk” for development of clinical depression will be offered a 12 week course, ‘Thoughts and Health’. This course aims to prevent first depression in adolescents. A comparable group of children will function as controls.

Depending on the type of variable, baseline comparisons between the two groups of relevant initial measures will be evaluated with t-tests or χ^2^ analyses. The effects of the programme on the development of clinical levels of depression will be evaluated using the follow-up data of 6, 12 and 18 months. Index parental depression at baseline will be tested as a moderator in the evaluation of the effects of the prevention programme.

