*Assessed and determined by a psychological assessment, based on the clinical rating instruments CDI, MINI-KID, RCADS and the children’s current status.

CDI, Children’s Depression Inventory; CGAS, Children’s Global Assessment Scale; MINI-KID, Mini International Neuropsychiatric Interview for Children and Adolescents.

Thus, about 20 students per course will be offered to participate in the intervention programme. These students will be approached by the programme staff and offered the opportunity to participate in the baseline clinical interview and assessment, the intervention programme, and postintervention follow-up assessments at 6, 12 and 18 months after programme completion (figure 1).

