#### Final junior high school grades, categorical variables (collected at approximately 18 months after course end)

Students’ final grades in junior high school (ie, in ninth grade, or 18 months after their inclusion in the programmes) will be collected to be able to evaluate the number of students who finish school with complete grades. The information will be provided by the school administration on consent (online supplemental file) from the students.

10.1136/bmjopen-2020-040374.supp1Supplementary data

All psychological assessments will be conducted by a trained psychologist from the primary care centre, and the focus groups and interviews will be conducted by the authors CW (PhD and specialist nurse) and PA (PhD student).

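### The dates given for the last 18-month follow-up (April 2021) and the primary analysis (May 2021) do not fit course II, which reaches 18 months in about March to June 2022

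*Protocol article*

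**What the plan says.** All references are to the protocol article.

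- **Courses.** Participants plans two, the first from about September 2019 and the second a year later: "course II beginning at the start of the fall semester (~1 September) 2020".
- **Follow-up clock.** Participants promises "postintervention follow-up assessments at 6, 12 and 18 months after programme completion".
- **Course length.** Intervention: prevention programme has the sessions "delivered two times per week for 2 weeks and then once a week for 8 weeks". The abstract says that at-risk children "will be offered a 12 week course". Table 2 puts the post-treatment assessment at 3 months.
- **Analysis timing.** Current trial status: "the last participant is expected to reach the primary endpoint (18-month follow-up) in April 2021. Primary data analysis will begin in May 2021". The sentence is not limited to one course. It is followed by a naturalistic follow-up phase lasting until October 2022.
- **Grades.** The outcome heading sets collection at about 18 months after the course ends. The text below it speaks of ninth grade, "or 18 months after their inclusion in the programmes".
- **Use of the data.** Statistical analysis fits a Cox model to the 6-, 12- and 18-month data. Discussion, questions 3 and 4, compares the arms on depressive symptoms and on school completion. Aim lists feasibility as primary and these two questions as secondary.

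**The concern.** The date given for the last participant's 18-month visit comes less than eight months after course II begins, so it cannot describe both courses. It is also the only statement in the article of when the analysis starts. Taken literally, it would open the analysis of questions 3 and 4 while one of the two courses is still early in follow-up and its students are still in eighth grade. The arm comparison would then rest largely on course I, or be repeated later on the full sample in a second analysis that the article does not describe. The sample is already small, and Participants says that no power calculation was made.

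**Working it through.** **Inputs.** Course starts are about 1 September 2019 and about 1 September 2020 (Participants). The session schedule gives 2 × 2 + 8 = 12 sessions in 2 + 8 = 10 weeks (Intervention). The abstract gives 12 weeks. Table 2's post-treatment point is 3 months, taken as 13 weeks.

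**Reproducing the stated date.** April 2021 minus 18 months is October 2019. That is shortly after course I starts, so the date fits course I counted from about inclusion. It fits course II on no clock.

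**Visit dates.** Visit date = course start + course length (0 if counted from course start) + 6, 12 or 18 months.

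| Clock starts at | Course I, 18 months | Course II, 6 months | Course II, 12 months | Course II, 18 months |
|---|---|---|---|---|
| Course start | 1 Mar 2021 | 1 Mar 2021 | 1 Sep 2021 | 1 Mar 2022 |
| Completion, 10 weeks | 10 May 2021 | 10 May 2021 | 10 Nov 2021 | 10 May 2022 |
| Completion, 12 weeks | 24 May 2021 | 24 May 2021 | 24 Nov 2021 | 24 May 2022 |
| Completion, 3 months | 1 Jun 2021 | 1 Jun 2021 | 1 Dec 2021 | 1 Jun 2022 |

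**Gap.** By calendar month, April 2021 to March 2022 is 11 months, to May 2022 is 13, and to June 2022 is 14. Even from the last day of April 2021 to 1 March 2022 the gap is 10 months.

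**What course II has by the end of April 2021.** It is about 7.9 months past its start and 4.9 to 5.6 months past completion. The 12- and 18-month visits are not due on any clock. The 6-month visit is not due on the completion clock, but would have been due on 1 March 2021 counted from course start.

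**Grades.** Course II recruits eighth graders in autumn 2020. They are still in eighth grade in May 2021 and finish ninth grade at the end of the 2021/22 school year. Course I students are then in ninth grade. Whether their final grades exist when analysis starts depends on the end date of the school year, which the article does not give.

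**Share of the sample.** By screening numbers, one course is 320/617 = 52%. By intervention places it is 20/40 = 50%, if the 40 per arm covers both courses. It is about half either way, if the courses are of similar size.

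**Precision.** With independent students, the standard error is proportional to 1/√n, so halving n multiplies it by √2 = 1.41. There are only two schools per arm. Adding course II at the same schools does not reduce between-school variance, so 1.41 is an upper bound for equal-sized courses.

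**The case against.** The strongest defence is that this is a short status paragraph and not an analysis rule. It says when analysis begins and sets no data cut. Neither Statistical analysis nor the Discussion excludes course II, and follow-up runs to October 2022, about 23.7 months after a 10 November 2020 completion, so course II's 18-month visit is covered. The dates may be a one-course timeline or a slip. The primary analysis could also mean feasibility, since Aim makes that primary, and course II's session surveys and post-course interviews would exist by May 2021.

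Much of this stands. A reader might infer that the trial plans to analyse questions 3 and 4 on half its sample, and the article does not say so. The defence does not remove the contradiction, however. The sentence calls the 18-month follow-up the primary endpoint and covers every participant. The naturalistic phase is named separately, after the primary endpoint and the primary analysis. If course II's 18-month visits belong to that phase, they fall outside the primary analysis as described.

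Other stronger readings are also unsupported:

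- **Course I grades.** A reader might conclude that these are missing too. That needs a school-year end date that the article does not give.
- **Course I date.** Counted from completion, course I also misses April 2021, by about a month. With an approximate start and an expected date, that is within rounding.
- **Exactly 20 of 40 per arm lost.** The 40 per arm may be per course, because it follows an expected 80 per course. The 20 per course describes the intervention programme only.
- **No 2021 comparison of arms at all.** Nothing in the article requires such a ban in a first, small study.

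**Conclusion.** The contradiction is certain: no clock or course length in the article brings course II to 18 months by April or May 2021. The stated date is 11 to 14 months too early for that course.

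The consequence is conditional. Only if the dates are kept would questions 3 and 4 be analysed without course II's 12- and 18-month data and its final grades, and without its 6-month data on the completion clock. The size, about half the sample and standard errors up to about 1.4 times larger, assumes courses of similar size and, for the upper figure, no between-school variance.

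This should be fixed, because it is the only stated timing for the analysis. It is not a fault in the design or the model, and a wording change removes it.

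**What to change.** 1. Choose one follow-up clock and use it in Participants, in the grades outcome and in Current trial status.
2. Restate the last 18-month follow-up on that clock: about May 2022 from programme completion, or about March 2022 from course start.
3. State that the arm comparison for questions 3 and 4 starts after course II's 18-month visits and the final ninth-grade grades of both cohorts are in. Both should fall inside the October 2022 end. The 18-month visits are due by about 1 June 2022, and the 2021/22 school year must end before the next autumn term, which by the article's calendar starts around 1 September.
4. If an analysis in 2021 is still wanted, label it interim and say that it covers feasibility, course I, or both.

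The cost is a wording change with no new visits or procedures. The downside is that the arm-comparison results come about a year later than now stated.
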